## Methods/design

### Study design

This will be an open-label, randomized, controlled trial. The study will recruit 86 obese patients with PCOS from Sichuan Women’s and Children’s Hospital, Sichuan Provincial Hospital of Traditional Chinese Medicine, the Third Affiliated Hospital of Chengdu University of Traditional Chinese Medicine, or Xinan Women’s and Children’s Hospital. The patients enrolled will be randomly assigned to a study group or a control group. The allocation ratio is 1:1, with 43 subjects in each group. All patients involved in this trial will be asked to sign the consent form before the intervention by researchers. Patients in the study group will be given acupuncture and clomiphene citrate treatment, and the control group will receive only clomiphene citrate treatment.

In addition, with the purpose to explore the mechanism of the differences in the individual curative effect of acupuncture, 10 subjects from each group will be selected in the order of enrollment for the metagenomic analysis. The selection criteria for these 10 subjects from each group will be that 5 of them with post-intervention LH/FSH levels of 1.0–1.5 and the other 5 subjects with post-intervention LH/FSH levels over 1.5. Meanwhile, ten healthy subjects who meet the study criteria will be recruited as the healthy control group and will not be given any intervention. The flow chart of the trial process is shown in Fig. 1. The research data collection is described in detail in Table 1.

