The metagenomic analysis will include 6 parts: (1) operational taxonomic units (OTUs): comparison the composition of intestinal microbiota at the level of phyla, classes, orders, families, genera, and species in each group; (2) alpha diversity: comparison the richness of species (the Chao 1 index), the abundance of the species (the Shannon-Wiener index and the Simpson index), and the evenness of the species (the Shannoneven index and the Simpsoneven index) in each group; (3) beta diversity: principal component analysis (PCA) and principal coordinate analysis (PCoA) will be used to identify the beta diversity in each group and hopefully to understand whether the differences in the microbiota compositions of groups are significant; (4) the taxonomic profile: comparison of the variety and relative abundance of taxon in the study group and control group at the level of phyla, classes, orders, families, genera, and species; (5) gene abundance profile: in order to identify the specific genes related to the individual curative effect differences of acupuncture, gene abundance will be profiled between the study group and control group, as well as within group (5 patients with post-intervention serum LH/FSH levels of 1.0–1.5 and 5 patients with serum LH/FSH levels over 1.5); (6) metagenomic biological pathways: selecting genes annotated by Kyoto Encyclopedia of Genes and Genomes (KEGG) to evaluate the functional aspects of the PCOS gut metagenome and hopefully to identify the metagenomic biological pathways contributing to the mechanism of individual curative effect differences of acupuncture for obese women with PCOS.

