### Statistical methods

Data will be analyzed using SPSS version 19.0 (SPSS 19.0, SPSS Inc., Chicago, IL, USA) by two qualified statisticians. Full analysis set (FAS), per-protocol analysis set (PPS), and safety set (SS) principles will be used to evaluate the final results. FAS is determined according to an intention-to-treat (ITT) population and includes all patients who have received at least one treatment. PPS will include all patients with good compliance who have completed the entire intervention. SS will include all patients who have received at least one intervention. The results of the measurement data analysis will be described using mean, median, 25th percentile, 75th percentile, standard deviation, maximum values, and minimum values. The comparison between the groups will be performed using the independent sample *t*-test or the Mann-Whitney *U* rank sum test according to whether the measurement data show a normal distribution and homogeneous variance. Frequency and constituent ratios will be used to describe enumeration data, and Pearson’s *χ*^2^ test or Fisher’s exact test will be used for group comparisons. Pearson correlations and Spearman correlations will be used to analyze the correlations between different indicators. All statistical tests will be considered statistically significant at *P <* 0.05 with a two-sided test. The gut microbiome will be analyzed using metagenomic analysis by BGI Shenzhen Co., Ltd (China).

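### The 5-versus-5 split on final LH/FSH does not measure response to acupuncture, and it is too small to identify genes

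*Protocol article*

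**What the plan says.** Study design, the note to Fig. 1, part (5) of the metagenomic analysis under Secondary outcomes, and Sample size all give the same rule. In each randomised arm, "10 subjects from each group will be selected in the order of enrollment for the metagenomic analysis". Five of them must have a final LH/FSH of 1.0–1.5, and "the other 5 subjects with post-intervention LH/FSH levels over 1.5". The rule is the same in the acupuncture-plus-clomiphene arm and the clomiphene-only arm.

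Part (5) gives the aim and the method: "in order to identify the specific genes related to the individual curative effect differences of acupuncture, gene abundance will be profiled". It names two comparisons: one arm against the other, and the 5-versus-5 comparison inside each arm.

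Related statements:
- Primary outcome: the change in LH/FSH, measured at baseline and after three cycles.
- Secondary outcomes: stool is taken at the first visit and at the end of the intervention.
- Secondary outcomes, part (3): PCA and PCoA are to be used, "hopefully to understand whether the differences in the microbiota compositions of groups are significant".
- Statistical methods: "All statistical tests will be considered statistically significant at" the two-sided 0.05 level. The next sentence gives the microbiome analysis to the sequencing company and names no gene-level test or threshold.
- Discussion: the small metagenomic sample is listed as a limitation.

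**The concern.** The trial's title and second aim concern why some patients respond to acupuncture and others do not. The only within-arm tool for that aim sorts patients by where they finish, not by how far they moved, and it does so in the same way whether or not they had acupuncture. No LH/FSH entry criterion exists, so starting values can differ widely. A patient going from 1.1 to 1.4 is placed in the better class, and one going from 3.0 to 1.6 in the worse.

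Genes that separate the two classes could therefore mark baseline severity, general prognosis or sensitivity to clomiphene, and still be reported as a mechanism of acupuncture response. With five patients per class, the comparison is also too small to single out genes in a metagenome-wide search.

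**Working it through.** **Inputs.** From the protocol: expected means 1.0 (study) and 1.6 (control), 37 per group, 80% power, alpha 0.05; cut-offs 1.0 and 1.5; 5 versus 5 within an arm. Not stated, so assumed: the SD, the baseline mean, the baseline–final correlation, the share of genes that truly differ, and the gene-level test.

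**1. The SD implied by the plan's own figure.** A two-sided t-test for a difference of 0.6 gives 37 per group when the SD is 0.897 to 0.908. With SD 0.9, d = 0.6/0.9 = 0.667 and n = 36.3, rounded up to 37. I use SD 0.9. The metagenomic 5 + 5 has no calculation to reproduce.

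**2. Who falls outside both classes.** Study arm, mean 1.0, SD 0.9:
- Normal: P(LH/FSH < 1.0) = 50%.
- Lognormal: log-variance = ln(1 + 0.9²) = 0.593 and log-mean = −0.297, so P(< 1.0) = Φ(0.297/0.770) = 65%.

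So half or more of the study arm, with the lowest final values, cannot enter the metagenomic sample.

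**3. Final level against change.** Illustration for the study arm: lognormal, final mean 1.0, SD 0.9 at both times, correlation 0.3 to 0.7, 10⁶ draws.

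| Assumed baseline mean | 1.0–1.5 class that did not fall | Over-1.5 class that did fall |
|---|---|---|
| 1.6 | 16–32% | 33–55% |
| 2.0 | 3–12% | 49–73% |
| 2.5 | 0.1–2% | 68–87% |

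The size of each error depends on the unstated baseline. In every row, a third or more of the worse class had in fact improved.

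**4. What the contrasts can show.** A high/low difference within the acupuncture arm combines prognosis, clomiphene response and acupuncture response. The same difference in the clomiphene-only arm contains the first two. Only the difference between these two differences bears on acupuncture, and the protocol states no such contrast.

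The 10-versus-10 comparison does not supply it, because both arms are filled to the same final mix. With the expected means and SD 0.9, the over-1.5 class is the top 18% (lognormal) to 29% (normal) of the study arm, but the top 44% to 54% of the control arm. The sampled patients are different slices of the two arms, so randomisation no longer protects the comparison.

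**5. What 5 versus 5 can detect.** There are C(10,5) = 252 arrangements.
- Smallest two-sided exact rank-sum P = 2/252 = 0.0079. Attained level at 0.05 = 8/252 = 0.032.
- Bonferroni: 0.05/m ≥ 0.0079 requires m ≤ 6 tests.
- Benjamini–Hochberg at 5%: a hit needs at least 0.0079/0.05 = 16% of all tested genes at the minimum P, or larger shares at the next attainable values (32% at or below 4/252 = 0.0159).
- t-test power at unadjusted 0.05: 29% for d = 1.0 and 79% for d = 2.0.
- No adjustment: 1,000 null genes give 1,000 × 0.032 = 32 (rank-sum) to 1,000 × 0.05 = 50 (t-test) false hits.

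**6. Share of hits that are false, without adjustment.** Share = (1−π)α / [(1−π)α + π × power], where π is the share of genes that truly differ. With d = 1.0, α = 0.05 and power 0.286:
- π = 1%: 0.0495/(0.0495 + 0.0029) = 94.5%.
- π = 20%: 0.0400/(0.0400 + 0.0573) = 41%.
- The share passes one half when π is below about 15%.

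**The case against.** - **The gene-level threshold is not clearly fixed.** The 0.05 sentence closes a paragraph on SPSS tests for clinical data, and the microbiome is then assigned elsewhere. A false discovery rate rule may sit in a document not shown, and its absence here is no error. This stands. But such a rule would not rescue the comparison: at 5 versus 5 it would leave almost nothing to declare.
- **A reader might infer that most reported genes would be false.** The protocol does not support this. It gives neither the share of truly different genes nor the effect sizes, and the result runs from 94.5% to 41% over plausible shares at one effect size. Nor does it name the rank-sum test for genes.
- **The plan also compares arms, and it samples stool at baseline.** Both are true. Saying that the plan ignores baseline is right only for the LH/FSH grouping. Because the same split is made in both arms, a between-arm contrast could be formed. It is not stated, and it would inherit the grouping and the selection on outcome.
- **The misclassification figures rest on an assumed baseline.** This stands, and they are illustrative only. That a final level differs from a change does not depend on them.
- **The small sample is acknowledged.** It is. The Discussion does not address the response definition, the excluded range or the missing contrast.
- **The PCA/PCoA wording is loose rather than a fixed test.** I agree that this is minor. Ordination displays distances and gives no significance test.

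**Conclusion.** The point holds in a limited form. The protocol fixes a grouping on the absolute final LH/FSH that does not measure response, departs from its own change-based primary outcome, and shuts out about 50% to 65% of the study arm under its own expected mean (SD 0.9 back-solved from the 37 per group). No stated contrast isolates acupuncture, and selection on the final value takes the between-arm comparison out of randomisation's protection. None of this depends on an unseen analysis plan, because the cut-offs, the 5 + 5 split and the purpose are written here.

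On size, 5 versus 5 cannot support gene identification under multiplicity control if a rank-sum test is used. Without control, it would give about 32 to 50 false hits per 1,000 null genes. The documents do not show that a majority of hits would be false, or that an unadjusted 0.05 rule definitely applies to genes.

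This should be changed, since it governs the aim in the title. It does not affect the primary clinical comparison.

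**What to change.** 1. Define response as change in log(LH/FSH) from baseline, kept continuous and adjusted for baseline.
2. Select patients for sequencing in order of enrolment among those who meet the metagenomic criteria, without the final-LH/FSH strata. Keep 10 per arm.
3. Over both arms, regress response on the baseline microbial feature, arm, and arm-by-feature interaction. The interaction is the term that addresses acupuncture.
4. Limit testing to a short list (alpha diversity, genera, KEGG pathways) with false discovery rate control. Label gene-level output descriptive and hypothesis-generating.
5. For beta diversity, use a distance-based permutation test such as PERMANOVA, and keep PCA and PCoA for display.
6. State that the 0.05 rule in Statistical methods does not serve as a gene-level threshold.

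**Cost.** Revised selection and analysis wording and a revised instruction to the sequencing company. The number sequenced does not change, and LH/FSH and stool are already collected at both times. There will be fewer genes to call significant, and an interaction estimated in about 20 patients stays exploratory with low power. If samples have already been chosen by the strata, changing the regression alone does not remove that selection, and the report should say so.

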### Adverse events

Adverse events of acupuncture mainly involve local ecchymoses, fainting, serious pain, and local infection, with close relevance to the subjective experience of patients and the penetration technique of acupuncturists. All the acupuncturists will undergo pretrial training and an entrance examination before the trial to ensure a safe operation. We will record any acupuncture-related adverse events that occur during the treatment, and operators will take necessary corresponding treatment measurements. In case of serious adverse events, the clinical trial will be interrupted immediately by investigators, and an effective treatment shall be taken. At the same time, the serious adverse events will be reported to the ethical review board in the hospital of Chengdu University of Traditional Chinese Medicine within 24 h. The whole process will be recorded in detail.

### Sample size

A previous study has found an average LH/FSH ratio for patients with PCOS after true acupuncture treatment of 1.4 [33]. Thus, we expect that the average LH/FSH ratio will be 1.0 in the study group and 1.6 in the control group. Assuming a power of 80% and a significance level of 0.05, 37 participants in each group will be required, as calculated using the *t*-test in G*Power. Based on a 15% dropout rate, 86 patients will be recruited, with no less than 43 participants in each group. Since there is no standard sample size calculation for metagenomic analysis at present, according to most of the studies about gut microbial studies for PCOS [44, 66], of the 86 participants, 10 patients in each group (5 patients with post-intervention serum LH/FSH levels of 1.0–1.5 and 5 patients with serum LH/FSH levels over 1.5) will be selected for metagenomic analysis.

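### The study-arm mean of 1.0 does not follow from the one cited figure of 1.4, so the 0.6 difference behind 37 per arm is unsupported as written; the dropout inflation is also slightly short.

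*Protocol article*

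**What the plan says.** The Sample size section of the protocol article opens with its only external evidence: "A previous study has found an average LH/FSH ratio for patients with PCOS after true acupuncture treatment of 1.4". The next sentence draws the planning values from it: "Thus, we expect that the average LH/FSH ratio will be 1.0 in the study group and 1.6 in the control group". The size follows: "Assuming a power of 80% and a significance level of 0.05, 37 participants in each group will be required", by a t-test in G*Power. Recruitment is then set: "Based on a 15% dropout rate, 86 patients will be recruited, with no less than 43 participants in each group".

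The article gives no SD or standardised effect, and no source for 1.0 or for 1.6. The Statistical methods section sets the significance level for all tests at "0.05 with a two-sided test", so the calculation is read here as two-sided.

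**The concern.** Two steps in the paragraph do not follow.

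- **The effect.** The word *Thus* presents 1.0 as a consequence of 1.4. The assumed study-arm mean is more favourable than the only figure offered in its support, and no argument bridges the gap. The difference of 0.6 is what turns into 37 per arm, so the stated 80% power depends on it.
- **The dropout allowance.** The recruited number should be the one that still leaves 37 per arm after 15% are lost. The stated 43 per arm does not quite do that.

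The first step matters more. If the trial finds no difference, the result will be reported as coming from a study with 80% power, and a reader cannot tell from the document why 0.6 was a reasonable difference to plan for.

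**Working it through.** **Inputs.** From Sample size: means 1.0 and 1.6 (difference 0.6), power 80%, significance level 0.05, 37 per arm, 15% dropout, 86 recruited (43 per arm), cited mean 1.4. From Statistical methods: two-sided testing. From Study design: 1:1 allocation.

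**1. Reproducing 86.**
- Multiplying: 37 × 1.15 = 42.55, rounded up to 43 per arm, 86 in total. This matches the plan exactly.
- Dividing, as the aim requires: 37 / 0.85 = 43.53, rounded up to 44 per arm, 88 in total.
- Completers expected at 15% dropout: 43 × 0.85 = 36.55 per arm; 86 × 0.85 = 73.1 in total, against 2 × 37 = 74 required.
- Dropout that 86 can absorb: 1 − 74/86 = 13.95%.

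**2. The SD implied by 37 per arm.** No SD is given, so 37 cannot be computed forward. For a two-sided two-sample t-test, power is taken from the noncentral t distribution with 2n − 2 degrees of freedom and noncentrality d × √(n/2), where d = difference / SD.
- 80% power at exactly n = 37 needs d = 0.660, so SD = 0.6 / 0.660 = 0.909.
- 80% power at exactly n = 36 needs d = 0.670, so SD = 0.6 / 0.670 = 0.896.
- Because n is rounded up, any SD from about 0.896 to 0.909 returns 37 per arm. An SD of 0.90 gives an exact n of 36.3, reported as 37. An SD of 0.91 gives 37.09, which would be reported as 38.

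**3. Power after 15% dropout, difference 0.6.**

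| SD | 36 per arm | 36.55 per arm | 37 per arm |
|---|---|---|---|
| 0.896 | 80.0% | 80.6% | 81.1% |
| 0.90 | 79.7% | 80.3% | 80.8% |
| 0.909 | 78.9% | 79.5% | 80.0% |

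The inflation error leaves power at about 79 to 81%, at worst about one point under the target.

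**4. Sensitivity to the difference.** Power at 37 per arm over the same SD range (0.909 to 0.896):

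| Difference | Power |
|---|---|
| 0.6 (planned) | 80 to 81% |
| 0.5 | 65 to 66% |
| 0.4 | 46 to 47% |
| 0.3 | 29 to 30% |
| 0.2 | 15 to 16% |

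The last row is the scenario in which the study arm reaches the cited 1.4 and the control arm the assumed 1.6: 1.6 − 1.4 = 0.2, one third of 0.6. For 80% power that difference would need about 317 to 326 per arm before dropout.

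**The case against.** Several points on the other side are sound.

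- **A reader might infer that the design misses its 80% power.** The documents do not support that. For every SD that returns 37 per arm, power at the expected 36.55 completers is 79.5 to 80.6%. Calling the design underpowered because of dropout would mean picking the least favourable SD in the range and rounding completers down in both arms. The inflation is still wrong as arithmetic, but by two patients.
- **A reader might infer that the evidence supports a difference of only 0.2, and that true power is about 15%.** That does not follow either. The 1.4 is one arm's mean from another study, which the Background describes as comparing true with sham acupuncture and for which it mentions no clomiphene. Here both arms take clomiphene. The cited study's comparator mean and SD are not in the document, and the 1.6 is this trial's own unsourced figure. Subtracting one from the other gives a scenario, not an estimate of the effect.
- **The SD is not given.** A journal article commonly leaves that to the full protocol, so its absence is not an error. It explains why 37 cannot be checked; it does not show that 37 is wrong.
- **Clomiphene might bring the study-arm mean below 1.4.** That is possible, but the article does not argue it, and clomiphene in both arms could lower the control mean as well.

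What these points leave untouched is the inference itself. The article states that 1.0 follows from 1.4, and it does not. This is something written, not something left to a fuller document.

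**Conclusion.** The point holds in a limited form. The planned difference of 0.6 is not supported by the evidence the protocol gives for it: 1.0 does not follow from 1.4, and 1.6 has no stated source. This does not show that 0.6 is wrong or that true power is below 80%. It shows that the 80% rests on an undocumented input to which power is very sensitive, falling to about 46 to 47% at a difference of 0.4 and about 15 to 16% at 0.2. Those figures assume a two-sided t-test and the SD of about 0.90 to 0.91 back-solved from 37 per arm; the 0.2 row also assumes that the control mean stays at 1.6.

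The dropout inflation is a definite but minor error: 43 per arm where division gives 44, about 73 completers where 74 are required, and a power loss of at most about one point.

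**What to change.** Keep 86 patients and reword the Sample size paragraph.

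1. Replace *Thus* with the actual basis for 1.0 and for 1.6, whether other data, clinical judgement or a smallest difference worth detecting.
2. State the SD that was actually entered in G*Power. The back-solved value must not be written in as if it were the sponsor's assumption; 0.91 in particular would return 38 per arm and contradict the stated 37.
3. Report power at differences smaller than 0.6, including the case of a study-arm mean of 1.4.
4. Correct the dropout sentence: either 86 patients cover dropout of up to about 14% (15% would need 88), or power at 15% dropout is about 79 to 81%, to be settled once the SD is stated.

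The cost is one rewritten paragraph and a slightly more cautious power statement. No extra patients and no change to the conduct of the trial are needed.

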### Randomization and allocation concealment

Patients will be randomly assigned to the study group or control group in a 1:1 ratio using a random number table. The random numbers will be provided by an independent statistician using the SPSS statistical software (version 19.0, SPSS Inc., Chicago, IL, USA). Random numbers and treatment protocols will be placed in sealed envelopes by an independent investigator. When a patient is enrolled, acupuncturists will check whether the envelope is sealed and then open the envelope to find the random number and treatment protocol for the patient.

### Blinding

As this is an open-label trial, neither the patients nor the acupuncturists will be blinded for the treatment. However, to eliminate potential bias, other researchers (including data collectors and statisticians) will be blinded.

### Data collection and management

Data collection will be conducted at baseline and post-intervention. Data collectors will record participant data on case report forms (CRFs). All data collectors will receive training on how to administer the SAS and SDS scales. After data collection using CRFs, we will use an electronic database for data entry and management. Two data collectors will perform double data entry, and completed clinical raw data will be forwarded to the supervisor of the project for review. The supervisor will correct any errors and export the data. After confirmation, the database will be locked and undergo statistical analysis. All data will be identified using participant numbers and stored in the database, which will be accessed using a password. The data will be monitored by the ethical review board of the Hospital of Chengdu University of Traditional Chinese Medicine.

The incidence of withdrawal from the study and the withdrawal reasons will be reported. Dropouts will be included in the analysis using modern imputation methods for missing data.

